### Study population

Participants will be recruited from Clemson University's student population, staff and faculty. Exclusion criteria will be applied (Table 1). We will balance the sample for sex/gender and will attempt mean matching for age, to yield roughly equal distributions in all combinations of the two between-persons predictors. Both sex/gender and age are possible confounds, as they may influence pain sensitivity [25, 26], placebo responsiveness [27] or the reception of the technology involved in the intervention [28].

**Table 1 Tab1:** Inclusion criteria for the proposed study

18 < Age < 64	
No past or present brain or nerve conditions (e.g. fainting, stroke, neuropathy)	
No past or present pain disorder (e.g. diagnosed migraine, chronic back pain)	
No open wounds or skin conditions on the dominant hand (e.g. hangnail, graze)	
Abstained from recreational drugs (alcohol, cannabis) for at least 24 h before the lab visit	
Abstained from pain medication (and other medication feasibly affecting experimental parameters) for at least 24 h before the lab visit	

Due to the deceptive nature of the protocol, full informed consent cannot be procured prior to participation; instead, a cover story will be presented to the participants. After the experiment, participants will receive full disclosure of the manipulation. Express permission will be asked of them to consider their data in the analysis. They will be given the choice to withdraw their data from analysis at any point prior to publication, without the need for justification.

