### Procedure

Participants will continually rate their pain during Sequence 1 under supervision of a laboratory assistant. They will then be randomly assigned to one of the 3(Metaphor)*x*2(Instruction) experimental groups. In a separate room, they will interact with the Metaphors delivering the Instructions. For the VEx and audio/text condition, interactional components are displayed in Fig. 2b. Crucially, neither assignment will be revealed to the laboratory assistant.

During the placebo manipulation, the inert medication will be automatically dispensed using a self-constructed pill dispenser controlled by an Arduino platform (https://www.arduino.cc/). For VEx and audio/text condition, pill dispension will be performed by the presentation software; in the HEx condition by pressing a button.

An overall inter-Sequence interval of 35 min will be observed for cutaneous sensitivity to recover, and to provide a plausible cover story for the medication to take effect (in the “medication” instruction).

The pain change at retest, compared between experimental groups, will be the main outcome.

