### Secondary measures

A number of putative predictors of pain sensitivity and placebo responsiveness [34] will be assessed before and during the experiment. These variables will be used as adjunct within- and between-persons predictors (covariates) of changes in pain sensitivity.

Psychological measures include pain questionnaires as well as several other psychological trait and state questionnaires (Table 2). Notably, participants will be asked about their desire for pain relief, and the expectation of pain relief after receiving the “medication” [5].

**Table 2 Tab2:** Putative predictors of pain sensitivity and placebo responsiveness

Questionnaire/scale	Construct	Example item
Trait questionnaires, answered in online survey before coming to the lab		
Pain Related Self Statements inventory (PRSS)	Coping with pain, catastrophizing about pain	“If I stay calm and relax, things will be better.”
Pain Vigilance and Awareness Questionnaire (PVAQ)	Attentional focus on pain	“I am quick to notice changes in location or extent of pain.”
Pain Sensitivity Questionnaire (PSQ)	Sensitivity to various painful stimuli	“Imagine you trap your finger in a drawer.”
Beliefs about Medicines Questionnaire (BMQ)	Attitudes towards medical profession and pharmaceutics	“Medicines do more harm than good.”
Beliefs in Expectation Biases	Beliefs to what extent perception is influenced by expectations	“In general, people are likely to experience the mood (good or bad) they expect to experience.”
International Personality Item Pool Big Five scales (IPIP B5)	Extraversion, agreeableness, conscientiousness, emotional stability, intelligence/imagination	“I feel comfortable around people.”
Internality, Powerful Others, and Chance scales (IPC)	Attribution of events to personal control, other individuals, chance	“Whether people act according to my wishes depends mainly on myself.”
Revised Life Orientation Test (LOT-R)	Positive/negative expectation of outcomes = dispositional optimism/pessimism	“I’m always optimistic about my future.”
State questionnaires, answered during the lab visit		
State Trait Anxiety Inventory (STAI)	Acute and general anxiety	“I get in a state of tension or turmoil as I think over my recent concerns and interests.”
Multidimensional Mood Questionnaire (MDMQ)	Good/bad mood, calmness/nervousness, wakefulness/tiredness	“Right now I feel […] content.”

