### Analysis and sample size estimation

Data entry is almost fully automated via the touch-screen interface (for continuous pain ratings), a digital survey tool (for other pain ratings and psychological measurements), and on-line registration of physiological parameters. The exception are blood pressure and temperature data which are documented on a score sheet. Continuous pain ratings will be recorded at a sampling rate of ca. 40 Hz, but downsampled to 1 s means for analysis.

Data will be analyzed with hierarchical linear modelling (HLM). Among other strengths, this approach enables us to consider both categorical and continuous predictor variables (e.g., covariates), and the inclusion of cases with missing values, allowing for the number of repeated measures to differ across persons [40]. HLM puts no constraints on the number of repeated measurements, which permits an analysis of differences in the time course of pain. HLM also allows for considering random effects (intercepts and slopes), suitable to the high interindividual variability of pain sensitivity [41].

The robustness of results will be assessed by outlier analyses of the regressional models provided by HLM, including contrasting of predicted versus actual values, studentized residuals and Mahalanobis’ distance. Outliers will be excluded both at the within-person level (individual measurement occasions) and the between-person level (exclusion of individuals with outliers). Robustness will be gauged by changes in the significance of the results.

HLM sample size estimation considers the sample size at level 1 (*n*; in our case, the repeated measurements within-persons) and the sample size at level 2 (*N*; in our case, the individual participants). Recommendations vary (e.g. [42, 43]); Hox [43] suggests larger sample sizes of *n* = 20 and *N* = 50 when investigating cross-level interactions. The wealth of data points provided by the second-by-second continuous pain ratings easily allow for meeting the *n* = 20 suggestion. However, while a total of 600 s of immersions will be available, the effective sample size will be lower due to large intraclass correlations, or strong autocorrelation. Due to the high interindividual variation of pain sensitivity, we would nevertheless aim for including *N* = 50 individual participants to determine difference between the six groups. Estimating 15 % attrition, the projected sample size therefore amounts to *N* = 58 individuals.

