### Hypotheses and expected results

The PE would be constituted by a larger symptom improvement from Sequence 1 to Sequence 2 in the “medication” Instruction, than in the “control/placebo” Instruction (“medication”(S2-S1)>“control”(S2-S1). This is a general test of the efficacy of the placebo paradigm, which is a crucial building block for assessing the effect of the different Metaphors.

The design does not strictly permit the establishment of equivalence between Metaphors in the sense of a non-inferiority trial, which is deemed too ambitious at this stage. For the proposed protocol, a non-significant difference between VEx and HEx would be considered as a first step to establish the viability of the VEx (HEx = VEx). On a descriptive level, we are expecting a slightly lower effect induced by the VEx, but lower variance than under the HEx, amounting to comparable effect sizes. Beyond that, it is hypothesized that the audio/text Metaphor induces a smaller symptom improvement than the other conditions (HEx = VEx > audio/text) due to absence of visual social cues.

Using a more fine grained analysis at the Trial level could yield additional information, such that groups differ in early or late Trials only, or that the slope (pain changes in consecutive Trials) is different between groups. For example, a significant difference between “medication” vs. “control” could come about by a shallower pain increase in consecutive Trials in Sequence 2, despite identical initial sensitivity (see Fig. 4).

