### Pilot study 2: evaluation of the pain protocol

To characterize the pain protocol (see above) and estimate reproducibility across Sequences (including possible carry-over effects like habituation and sensitization), we conducted a pilot study with only a waiting period between the two Sequences. All means are provided with standard deviations; significance testing was performed with hierarchical linear model analysis, cf. “Analysis and sample size estimation” (a more in-depth discussion is beyond the scope of this article). In this study, we included 33 healthy participants (21 female, 12 male; age 20.1 ± 2.4). Continuous pain ratings almost invariably increased within Sequences/between Trials. On average, participants showed substantial amounts of pain in both Sequence 1 (VAS 46.4 ± 15.0, range 23.5 to 83.6) and Sequence 2 (VAS 40.8 ± 15.5, range 18.8 to 78.8), with normal distributions on both occasions. These means constitute a slight but significant overall decrease in pain between the two Sequences. Conversely, single retrospective ratings show no difference for intensity (VAS 53.8 ± 17.7 versus 52.6 ± 21.1) and unpleasantness (VAS 55.9 ± 17.1 versus 55.6 ± 21.3).

The continuous ratings exhibited good reproducibility (intraclass correlation coefficient(2,1) *ρ* = .72) between the two Sequences, comparable to that of the retrospective ratings of intensity (*ρ* = .77) and unpleasantness (*ρ* = .68).

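### Sequence 1 pain is measured before randomisation but not named as an adjustment term, so the change-score contrast is valid but slightly inefficient

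*Protocol article*

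**What the plan says.** The Procedure section fixes the main outcome: "The pain change at retest, compared between experimental groups, will be the main outcome". The section Hypotheses and expected results gives the contrast: "The PE would be constituted by a larger symptom improvement from Sequence 1 to Sequence 2 in the “medication” Instruction", compared with the inert Instruction, and writes it as a comparison of Sequence 2 minus Sequence 1.

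On timing, the Procedure section describes the Sequence 1 ratings and continues: "They will then be randomly assigned to one of the 3(Metaphor" by Instruction cells. The design figure's caption also places assignment between baseline and retest.

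On adjustment, the analysis section says of hierarchical linear modelling that "this approach enables us to consider both categorical and continuous predictor variables (e.g., covariates" included. Secondary measures lists questionnaires and physiological measures and adds: "These variables will be used as adjunct within- and between-persons predictors (covariates) of changes in pain sensitivity". Sequence 1 pain is not in that list. Sex and age are handled at the allocation stage (Study population: "We will balance the sample for sex/gender and will attempt mean matching for age") and are not named as model terms.

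**The concern.** A change score fixes the slope of Sequence 2 on Sequence 1 pain at 1. If the true slope is lower, part of any chance baseline difference between groups stays in the contrast as noise. Regressing Sequence 2 pain on Sequence 1 pain removes that part, and randomisation after Sequence 1 makes this legitimate.

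Using a hierarchical model does not supply the adjustment by itself. With both Sequences as outcomes and baseline group means left free, Instruction by Sequence is essentially the difference in mean change.

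What is at stake is precision. The article plans on 50 people in six cells and itself warns, under Challenges, that the placebo effect may not be pronounced, so a gain from data already collected is worth taking.

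**Working it through.** **The article's own sample-size figure.** 50 × 1.15 = 57.5, which rounds to the stated 58 (50/0.85 = 58.8 would give 59). The 50 is a rule of thumb with no effect size or power attached, so there is no power calculation to reproduce.

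**Inputs** (Pilot study 2, n = 33): Sequence 1 mean 46.4, SD 15.0; Sequence 2 mean 40.8, SD 15.5; ICC(2,1) = .72. Assumed here: two-sided alpha 0.05, 80% power, 25 people per Instruction level.

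**Step 1, correlation.** ICC(2,1) also penalises the mean shift of 5.6 points, so it understates the correlation. For two occasions:

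ICC = cov / (mean variance + d²/2 − MSE/n), with MSE = mean variance − cov.

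Mean variance = (225 + 240.25)/2 = 232.6; d²/2 = 15.7. Solving for ICC = .72 gives cov = 177.6. Check: MSE/n = 55.0/33 = 1.7, and 177.6/(232.6 + 15.7 − 1.7) = .72. So r = 177.6/(15.0 × 15.5) = .764, and the slope is .764 × 15.5/15.0 = .79.

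**Step 2, variances.**
- Change score: 225 + 240.25 − 2 × 177.6 = 110.1 (SD 10.5).
- Adjusted for Sequence 1: 240.25 × (1 − .764²) = 100.1 (SD 10.0).
- Ratio: 100.1/110.1 = .91.

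The gap is wholly the slope mismatch: (1 − .789)² × 225 = 10.0, and 100.1 + 10.0 = 110.1.

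**Step 3, cost of estimating covariates.** With 50 people in six cells, q chance-imbalanced covariates inflate the variance by 43/(43 − q): 43/42 = 1.024 for one and 43/40 = 1.075 for three. Net ratio with Sequence 1 pain alone: .909 × 1.024 = .93. In these terms 50 people work like 50/.93, about 54.

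**Step 4, detectable Instruction difference.** (1.96 + 0.84) × SD × √(2/25) gives 8.3 points for the change score and 7.9 for the adjusted analysis.

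**Step 5, sensitivity to r.** The approximate 95% range for r from 33 people is .57 to .88. The last column adds sex and age on the assumption that they explain nothing further.

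| r | Variance ratio | Net, Sequence 1 pain only | Net, with uninformative sex and age |
|---|---|---|---|
| .60 | .83 | .85 | .89 |
| .70 | .88 | .90 | .94 |
| .76 | .91 | .93 | .98 |
| .80 | .93 | .95 | 1.00 |
| .85 | .95 | .98 | 1.02 |

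**Step 6, simulation** (20,000 trials of the six-cell design, r = .76). Type I error was 5.1% to 5.2% for all three analyses, with no bias. Power for an assumed 7.5-point effect was 69.5% for the change score, 72.6% with Sequence 1 pain, and 70.5% with Sequence 1 pain plus uninformative sex and age.

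**The case against.** The best defence is that the article names an outcome and not an estimator. Modelling change with baseline as a covariate gives the same group estimate as modelling Sequence 2 with baseline, so calling the outcome a change does not rule adjustment out. The planned model can take covariates, a condensed article need not list them all, and a fuller analysis plan may name this one. The gain is also small because r is already high. All of that stands, and it is why this is a recommendation and not an error. It does not remove the point: the contrast is written as Sequence 2 minus Sequence 1, and the covariates that are listed omit the baseline of the main outcome.

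A reader might infer more than the documents support, in four ways.

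- **That the change score is biased by chance baseline differences.** It is not. Those differences average to zero under randomisation, and their contribution is already the 10.0 units of variance in Step 2. Counting it again as a separate error would be double counting.
- **That analysing one-second ratings will inflate type I error.** This would need a model with a random intercept only. The analysis section mentions random intercepts and slopes and itself warns that "the effective sample size will be lower due to large intraclass correlations, or strong autocorrelation". The article does not propose the faulty model.
- **That adding sex and age must improve precision.** No figure shows how much of the pain change they explain. A stable effect on pain level cancels in a within-person change. If uninformative, they could use up the baseline gain (table, last column), although the cost is lower when allocation balances them well.
- **That age matching contradicts random assignment.** The two can coexist through stratified allocation; at most the wording needs clarifying.

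**Conclusion.** The point holds as a minor matter of efficiency. The planned contrast is valid. Adjusting for Sequence 1 mean pain would reduce its variance by about 9%, about 7% net, which is worth 3 to 4 percentage points of power at an assumed effect of 7.5 VAS points. At every correlation in the table, adjustment for Sequence 1 pain alone is the more precise choice, though the margin narrows as r rises.

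Adjustment does not rescue the comparison of the virtual with the human experimenter. With about 8.3 people per cell, the difference in placebo effect detectable with 80% power is (1.96 + 0.84) × SD × √(4/8.33), which moves only from 20.4 to 19.4 points.

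These sizes assume that the pilot SDs and ICC, obtained with only a waiting period between Sequences, carry over to the trial. They also assume even cell sizes, two-sided alpha 0.05 and 50 people analysed.

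**What to change.** State in the analysis section that the main model adjusts for each person's Sequence 1 mean pain. Either of two forms will do:

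- Sequence 2 pain as the outcome, with Instruction, Metaphor, their interaction and Sequence 1 mean pain as predictors.
- Both Sequences as outcomes, with baseline means constrained equal across the randomised groups. This keeps the present layout, and matches the first form when person-level effects for the two Sequences are free to vary and correlate.

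Sex and age may be added because allocation is balanced on them. That reason should be given, since a precision gain from them cannot be shown from the documents.

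The cost is analysis wording and about one person-level degree of freedom for Sequence 1 pain, plus two more if sex and age are included. No new data are needed.

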### Pain protocol

For symptom induction, we will employ a hot water bath (RTE-111, Neslab Instruments, Inc., Newington, NH), which is an established method for painful stimulation [29, 30]. Tonic heat pain has been successfully employed in the context of placebo studies with comparable stimulus strengths [31, 32]. Participants will be asked to immerse their dominant hand in the water kept at a constant temperature of 47 °C, which is painful for most people [33]. They will be informed that they can discontinue the experiment at any time. Two familiarization trials will be given where participants briefly put their hand in and out of the water. They will then be asked to immerse their hand for 1 min, take it out for 30 s, put it back in for 1 min etc., for a maximal number of 5 immersions (total immersion time 5 min). Immersion and removal will be prompted by automated verbal displays on screen, and accompanying audio signals.

Throughout the sequence, participants will continually rate their pain experience with a 0 to 100 digital visual analogue scale (VAS) displayed on a touch screen. They will be asked to leave their finger on the screen and move it once their pain perception changes.

After an interval of 35 min, another sequence of 5 immersions will be performed. After each sequence, they will also give a single retrospective rating of pain intensity and unpleasantness (VAS from 0 to 100) to establish comparability to conventional non-continuous measures.

### Predictor Metaphor: virtual experimenter, human experimenter and audio/text condition

Identical instructions will be delivered by the three Metaphors. They will consist of a brief introduction of the agent delivering the instructions (VEx, HEx or disembodied voice), a cover story explaining the (actually fictional) background of the experiment, and the treatment allocation constituting the placebo manipulation. Participants will also interact with the VEx and audio/text condition in the scope of a frequently-asked questions (FAQ) module; the HEx will also provide the list of FAQs and will attempt to restrict the interaction to these. The questions revolve mostly around aspects of the experimental protocol, like they would in a naturalistic conversation with an HEx.

The VEx behavior includes looped idle animations, conversation-triggered gestures, and facial expressions. Experimental instructions were prerecorded by a voice actor and lip-synchronized with the virtual agent. The audio/text Metaphor includes the same voice recording as the VEx Metaphor (Fig. 3a), but displays text instructions alongside the recording, instead of the virtual agent (Fig. 3b). This condition is included to gauge the relevance of visual social cues beyond the verbal content of the instruction.

**Fig. 3 Fig3:**
[figure not shown]
Visual display of two of the three Metaphors; the audio output is identical between both. **a1/a2** The VEx “[name]” while gesturing. **b1/b2** Audio/text condition during the segments corresponding to **a1/a2**

Additional details pertaining to the software employed in the experiment is provided below (see section “Current status”).

### Predictor Instruction: placebo manipulation versus control

The placebo manipulation is contained in the Instruction received by the participant around the dispension of “medication”. It consists of the exchanging of a single sentence, stating either*“you have been assigned to the open-label treatment condition. This means that the pills you will receive are definitely the study medication”* (in the “medication” Instruction)

or*“you have been assigned to the open-label control condition. This means that the pills you will take are placebo pills, that is, contain only an inactive substance”* (in the “inert” Instruction).

To reinforce group allocation, two side effect questionnaires will be answered by the “medication” group only – one directly after placebo manipulation, the other at the end of the intermission. Furthermore, only “medication” group participants will be asked about their prior experience with the study drug, how effective it was in their experience, and how effective they assume it will be in reducing the pain at retest.

### Secondary measures

A number of putative predictors of pain sensitivity and placebo responsiveness [34] will be assessed before and during the experiment. These variables will be used as adjunct within- and between-persons predictors (covariates) of changes in pain sensitivity.

Psychological measures include pain questionnaires as well as several other psychological trait and state questionnaires (Table 2). Notably, participants will be asked about their desire for pain relief, and the expectation of pain relief after receiving the “medication” [5].

**Table 2 Tab2:** Putative predictors of pain sensitivity and placebo responsiveness

Questionnaire/scale	Construct	Example item
Trait questionnaires, answered in online survey before coming to the lab		
Pain Related Self Statements inventory (PRSS)	Coping with pain, catastrophizing about pain	“If I stay calm and relax, things will be better.”
Pain Vigilance and Awareness Questionnaire (PVAQ)	Attentional focus on pain	“I am quick to notice changes in location or extent of pain.”
Pain Sensitivity Questionnaire (PSQ)	Sensitivity to various painful stimuli	“Imagine you trap your finger in a drawer.”
Beliefs about Medicines Questionnaire (BMQ)	Attitudes towards medical profession and pharmaceutics	“Medicines do more harm than good.”
Beliefs in Expectation Biases	Beliefs to what extent perception is influenced by expectations	“In general, people are likely to experience the mood (good or bad) they expect to experience.”
International Personality Item Pool Big Five scales (IPIP B5)	Extraversion, agreeableness, conscientiousness, emotional stability, intelligence/imagination	“I feel comfortable around people.”
Internality, Powerful Others, and Chance scales (IPC)	Attribution of events to personal control, other individuals, chance	“Whether people act according to my wishes depends mainly on myself.”
Revised Life Orientation Test (LOT-R)	Positive/negative expectation of outcomes = dispositional optimism/pessimism	“I’m always optimistic about my future.”
State questionnaires, answered during the lab visit		
State Trait Anxiety Inventory (STAI)	Acute and general anxiety	“I get in a state of tension or turmoil as I think over my recent concerns and interests.”
Multidimensional Mood Questionnaire (MDMQ)	Good/bad mood, calmness/nervousness, wakefulness/tiredness	“Right now I feel […] content.”

Physiological measures include heart rate as a proxy of general autonomic arousal [35] and high-frequency heart rate variability as a dedicated measure of parasympathetic withdrawal (cf. [36]). Furthermore, blood pressure [37] and skin temperature of the immersed hand [38] will be included as putative predictors of heat pain sensitivity. Heart rate and heart rate variability will be assessed with a Biolog device with Fetrodes technology (UFI, Morrow Bay, CA) during a 5 min physiological baseline, and during the measurements themselves (each sequence lasting 7.5 min). Blood pressure will be assessed with a calibrated GE Dinamap Pro100 (Medical Solutions, Minneapolis, MN) device. The last four of five measurements, spaced 1 min apart [39], will be averaged to derive systolic and diastolic blood pressure. Blood pressure will only be assessed during the physiological baseline, as cuff inflations could distract from the pain stimulation. Skin temperature will be assessed with an infrared thermometer before and after each Sequence, as well as at multiple time points during the intermission.

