## Background

To a large extent, placebo effects arise from the psychosocial setting in which a treatment is delivered, most notably the physician/patient or experimenter/participant interaction [1]. These effects can be substantial [2, 3]. However, it is difficult to systematically tease apart the contributions made by separate aspects of an interaction. In this paper, we propose the use of a virtual experimenter as a platform to address these issues with minimized risk of bias.

We define the placebo effect (PE) as that part of an actually experienced symptom improvement mediated by psychological expectancy concerning a treatment, regardless of the treatment’s actual efficacy [4]. This expectancy arises from multiple sources in the treatment’s psychosocial context, such as verbal instruction [5], conditioning [6] or social learning [7].

PEs are most well known in the context of randomized clinical trials, where the placebo group receives an inert treatment to serve as control for the actual treatment [8]. However, the change happening in the placebo group is always a composite measure, including the actual placebo effect and numerous other factors [9, 10]. Some of these are a feature of the nosological subject matter, such as the natural course of disease and the fact that people tend to seek out treatment at peaks of symptom severity. These factors can lead to regression to the mean, which describes the fact that extreme values will tend to converge toward less extreme values at retest. Other factors include distinct psychological phenomena, like response biases, which cause study participants to modify their answering behavior after receiving a placebo treatment, without actually affecting their symptom experience [9, 10].

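### Measures taken after the Instruction, including expected relief, are given the same covariate role for pain change as baseline measures; any Instruction or Metaphor model that used them would understate the effect

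*Protocol article*

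**What the plan says.** Under Secondary measures, the putative predictors of pain sensitivity and placebo responsiveness "will be assessed before and during the experiment". Their role follows: "These variables will be used as adjunct within- and between-persons predictors (covariates) of changes in pain sensitivity". The section singles out two of them: "participants will be asked about their desire for pain relief, and the expectation of pain relief after receiving the" so-called medication. It then adds heart rate and heart rate variability, recorded "during a 5 min physiological baseline, and during the measurements themselves", and skin temperature, taken around each Sequence and repeatedly in the intermission. Blood pressure is taken at baseline only, and most of Table 2 is trait questionnaires completed online before the visit.

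Under Procedure, assignment comes after Sequence 1, and the main outcome is the change in pain at retest, compared between groups. Under Predictor Instruction, "only “medication” group participants will be asked about their prior experience with the study drug", and the same restriction covers "how effective they assume it will be in reducing the pain at retest".

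The Background defines the placebo effect as "that part of an actually experienced symptom improvement mediated by psychological expectancy concerning a treatment".

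**The concern.** A covariate that the intervention can change is not a baseline covariate. Expected relief is asked after the pill has been presented as active or inert, and moving that expectation is the purpose of the Instruction. By the article's own definition it is the route through which the placebo effect runs. Holding it fixed while estimating the Instruction effect removes the part of the contrast that the study sets out to measure.

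The Metaphor comparison is exposed in the same way. If the human experimenter, the virtual experimenter and the audio/text display differ in the expectancy they raise, adjusting for expectancy shrinks that difference. The Hypotheses section treats a non-significant difference between virtual and human experimenter as a first step towards viability, so the shrinkage would favour the hoped-for conclusion.

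Heart rate and its variability in Sequence 2 are recorded alongside the outcome and may respond to the Instruction or to the pain itself. Skin temperature after assignment is less obviously affected, but its timing places it in the same class.

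There is also a data problem. If the expectancy covariate is the question put only to the medication group, it is missing for everyone in the inert group.

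**Working it through.** **Plan figures.** The article gives no effect size, alpha or power, so there is no stated figure on this point to reproduce. Its recruitment figure of 58 matches 50 × 1.15 = 57.5, rounded up (50 / 0.85 = 58.8 would give 59). Nothing below depends on it.

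**Timing.**
- Before the Instruction: trait questionnaires, baseline blood pressure, the 5-minute physiological baseline, and Sequence 1 pain, heart rate and skin temperature.
- After it: expected relief, Sequence 2 heart rate and heart rate variability, and skin temperature in the intermission and around Sequence 2.
- Not stated relative to the Instruction: desire for relief and the state scales (STAI, MDMQ).

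**Inputs from the article.** N = 50 evaluable, taken as 25 per Instruction group. Pilot study 2: SD 15.0 (Sequence 1) and 15.5 (Sequence 2), intraclass correlation 0.72, used here as an approximate correlation.

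**Assumptions, for illustration only.** Total Instruction effect of −10 VAS points on change, two-sided 5% test, and expectancy measured without error in both groups and shifted by a = 1.5 or 2 within-group SDs. The hierarchical model is simplified to a regression on each person's change score.

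**Step 1: SD of change.** √(15.0² + 15.5² − 2 × 0.72 × 15.0 × 15.5) = √(225 + 240.25 − 334.8) = √130.45 = 11.4.

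**Step 2: no post-instruction covariate.** SE = 11.42 × √(2/25) = 3.23. Power is 0.87 by formula and about 0.86 by simulation (4,000 runs).

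**Step 3: expectancy added.** If a share m of the effect is mediated, the adjusted coefficient is −10 × (1 − m). With equal groups, overlap between Instruction and expectancy multiplies the SE by √(1 + a²/4): 1.25 for a = 1.5 and 1.41 for a = 2. This is partly offset when expectancy explains residual variance. With no mediation, the SE is 3.23 × 1.25 = 4.04 or 3.23 × 1.41 = 4.57 (simulated 4.08 and 4.64).

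| Share mediated | Adjusted estimate | Rejection rate, a = 1.5 | Rejection rate, a = 2 |
|---|---|---|---|
| None | about −10 | 0.66 | 0.56 |
| Half | about −5 | 0.24 | 0.20 |
| All | about 0 | 0.05 | 0.05 |

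**Step 4: expectancy recorded in the medication group only.** Complete cases are 25 of 50, none of them inert. The Instruction column then equals the intercept, so the design matrix (intercept, Instruction, expectancy) has rank 2 of 3 and the Instruction effect cannot be estimated. The Analysis section's remark that hierarchical modelling includes cases with missing values concerns unequal numbers of repeated measures per person. It does not cover a person-level covariate absent for a whole group.

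**The case against.** The strongest reply is that no adjusted main test is specified. The Procedure and Hypotheses sections state the main contrast as a difference in change between groups, with no covariates. The Analysis section mentions covariates only as something the method can accommodate. The sentence at issue sits under Secondary measures and calls the predictors adjunct. Expectancy as a predictor of responsiveness could be studied within the medication group or in a separate model, and neither would bias the Instruction contrast. This stands. A reader might infer that the plan does adjust away the placebo effect or does drop the inert group; the documents do not say so. What remains is that the covariate role is stated for the same change that forms the main outcome, and no later measure is excluded.

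Second, the two sections may describe two questions. Secondary measures speaks of participants in general, while Predictor Instruction restricts an efficacy question to one group. If expectation is asked of everyone, no group is lost, although the mediator problem remains. The two harms are therefore alternatives for any one item.

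Third, a reader might infer that all the scores will be entered at once or screened one by one, with lost degrees of freedom and chance findings. The article proposes neither, and most of the scores are legitimate pre-visit covariates.

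**Conclusion.** The point holds as a defect in how the covariate role is assigned, not as proof that the main test is biased. If post-instruction expectancy enters a model that estimates the Instruction or Metaphor effect, the estimate is attenuated in proportion to the share mediated. In the illustration, power falls from about 0.86 to between 0.20 and 0.24 at half mediation, and to the 5% error rate at full mediation. Even with no mediation it falls to between 0.56 and 0.66, through collinearity alone. If the item asked of one group is used, the Instruction effect is not estimable in that model.

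The direction rests on the article's own definition; the sizes rest on the assumed effect, expectancy shift and test level. A reader might infer that the adjusted effect must be zero whatever the true placebo effect. That needs the whole Instruction contrast to run through expectancy, expectancy to be well measured, and no confounding between expectancy and pain. The Background defines the placebo effect as the expectancy-mediated part of improvement and lists response bias as a separate source of reported change, so partial attenuation is the safer expectation. No size can be put on the physiological measures from the documents.

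**What to change.** State that models estimating Instruction and Metaphor effects use only pre-instruction covariates: for example sex, age, trait questionnaires and baseline physiology, with Sequence 1 pain as the baseline. Give the timing of the state scales and of the desire-for-relief question, and class them accordingly. Move expected relief, Sequence 2 heart rate and heart rate variability, and post-assignment skin temperature to separate exploratory mediation models. Analyse any item asked of one group only within the medication group.

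Reconcile Secondary measures with Predictor Instruction on who is asked about expectation, and say whether these are one item or two. Simply extending the medication-only question to the inert group is not a free remedy. It is introduced alongside steps meant to reinforce allocation, so asking it of inert participants could alter the control condition.

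The cost is a few sentences and no new data. The one downside is that covariates measured after the Instruction can no longer sharpen the main model.
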